## Abstract

**Introduction:**

Acute kidney injury (AKI) contributes to morbidity and mortality, and its care is often suboptimal and/or delayed. The Acute Kidney Outreach to Reduce Deterioration and Death (AKORDD) study is a large pilot testing provision of early specialist advice, to improve outcomes for patients with AKI.

**Methods and analysis:**

This before and after study will test an Outreach service for adult patients with AKI, identified using the national algorithm. During the 2-month before phase, AKI outcomes (30-day mortality, need for dialysis or AKI stage deterioration) will be observed in the intervention and control hospitals and their respective community areas; no interventions will be delivered. Patients will receive good standard care. During the 5-month after phase, the intervention will be delivered to patients with AKI in the intervention hospital and its area. Patients with AKI in the control hospital and its area will continue to have good standard care only. Patients already on dialysis and at end of life will be excluded. The interventions will be initially delivered via a phone call, with or without a visit to the primary clinician, aiming at rapidly establishing the aetiology, correcting reversible causes and conducting further appropriate investigation. Surviving stage 3 patients will be followed-up in an AKI clinic. We will conduct qualitative research using focus group-based discussions with primary and secondary care clinicians during the early and late phases of the trial. This will help break down potential barriers and improve care delivery.

**Ethics and dissemination:**

Patients will be contacted about the study allowing them to ‘opt out’. The work of an Outreach team, guided by AKI alerts and delivering timely advice to clinicians, may improve outcomes. If the results suggest that benefits are delivered by an AKI Outreach team, this study will lead to a full cluster randomised trial.

**Trial registration number:**

NCT02398682: Pre-results.

Strengths and limitations of this studyAcute Kidney Outreach to Reduce Deterioration and Death (AKORDD) is a large pilot study and the first controlled trial in unselected acute kidney injury (AKI) in the UK.It employs a before and after design in control and intervention hospitals and their areas.It uses the national AKI algorithm in hospital and community to identify cases.The intervention is delivered by the Outreach team for all eligible cases in working hours.With only two sites, it is not a full cluster randomised study.

## Background and rationale

Acute kidney injury (AKI) is a common condition. Its prevalence in UK is estimated to be >20% of emergency admissions.^1^ Worldwide incidence is about 21.6% in adults in hospital settings, as shown in a recent meta-analysis.^2^ Mortality due to AKI is high. Recent studies show an overall mortality of >23% in the UK,^3^ and a similar percentage worldwide.^2^ There are recognised deficiencies in the clinical care of patients with AKI.^4^ The UK's National Confidential Enquiry into Patient Outcome and Death (NCEPOD)^4^ showed that 14% of fatal AKI cases were avoidable. One large UK study found that mortality in patients with AKI was significantly higher in the 55% of acute trusts that did not have onsite renal teams.^5^ AKI aetiology is diverse, and it usually occurs in the setting of other comorbidities. However, few studies have looked into the effect of non-renal comorbidities on outcome. Charlson comorbidities have been used to predict outcome in end-stage renal disease.^6–8^ Our previous work examined the role of comorbidity in AKI, demonstrating the impact of solid and haematological malignancies, as well as the total burden of non-malignant comorbidities.^9^ Intensive care patients with AKI and uncontrolled malignancy are known to have poor outcome.^10^

Advances in technology show promise in the early identification of AKI, using electronic alerts.^9^
^11^ Theoretically, bringing the recent rise in creatinine to clinicians' attention should prompt improvements in management. However, a recent study using alerts alone failed to demonstrate any improvements in outcome.^12^

The concept of an Outreach team has been established in critical care for many years, offering rapid assessment to deteriorating patients. One large cluster randomised trial (CRT) failed to show a significant impact of Medical Emergency Team in reducing hospital cardiac arrests.^13^ In the UK, the introduction of critical care Outreach in an 800-bed general hospital significantly reduced mortality.^14^ Two large meta-analyses were conducted analysing trials of rapid response teams (RRTs). Outreach teams were successful in reducing non-intensive care unit cardiac arrest by 34%, but mortality was not significantly reduced.^15^ Overcoming the barriers to implementation of the RRT service would further improve outcome.^16^ The dissociation between decline of cardiac arrest rates and mortality is not fully understood.

The use of an Outreach team for renal patients is novel. We piloted a renal Outreach team in 2009, offering early specialist advice for patients who developed AKI. The team delivered limited dose (3 hours a day, 5 days/week) telephone advice to clinicians looking after patients with AKI. Two hundred and sixty-two alerts were identified with a successful telephone call in 88% of the cases. Considerable numbers of recommendations were made. These included optimisation of fluid status and medication management.^17^ There has also been one other, smaller pilot of early intervention in AKI.^18^

The adverse sequelae of an AKI episode continue even after its complete or partial resolution. It may be valuable to have early renal follow-up, especially for severe cases. A retrospective study suggested that early follow-up of patients with AKI, especially those not previously known to nephrology services, may reduce mortality.^19^

The true cost of AKI is unknown as existing studies are retrospective. Calculating the cost of AKI syndrome is important to assess the burden to the healthcare systems. The healthcare costs for patients with AKI have a robust relationship to the severity of AKI.^20^ It was estimated in previous studies that prevention of 30% of AKI cases would save the National Health Service (NHS) between £130 and £186 million per year.^21^ In a European study, it was shown that conservative management of AKI, including the initial hospitalisation and 2-year follow-up, incurred average costs of €34 000, and this increased to €40 000–€55 000 if a patient had dialysis (depending on the modality).^22^ The financial burden includes inpatient, critical care and postdischarge costs (the latter encompass progression of chronic kidney disease (CKD) with or without renal replacement therapy).^21^

Overall, the study's primary aim is to test the feasibility, systems for and value of the Outreach team approach on the measured outcomes in patients with AKI, before a planned CRT.

## Methods

### Overall study design

We will run a quasi-experimental trial of a complex multifactorial intervention.^23^ Using a before and after study design, we will pilot the Outreach service to patients with AKI. Patients will be recruited once they have an electronic alert indicating that they have AKI. Inclusion and exclusion criteria will then be applied (box 1). There will be no patient-level randomisation to avoid the risk of contamination, as this is a pilot for a CRT. The study has been approved by (1) the National Research Ethics Service (Reference: 14/EM/0184, NRES Committee East Midlands—Nottingham 1, approved 22 May 2014) and (2) the Confidentiality Advisory Group (CAG Reference: CAG 2-07(a)/2014—approved 30 May 2014).
Box 1Inclusion and exclusion criteria for the Acute Kidney Outreach to Reduce Deterioration and Death (AKORDD) studyInclusion criteria:Adult (≥18 years) patients with an alert due to AKI from a blood test arising from Heartlands or Good Hope Hospitals (and their associated postcodes for outpatients/primary care).AKI stage 1, 2 or 3.Exclusion criteria:Patient deceased at the time of Outreach team intervention.Patient already accepted for dialysis by HEFT renal unit.Known dialysis/end-stage renal disease patients (excluded from alerts).Other patients with stable chronic kidney disease (definition of stable CKD), or progressive CKD where there is no obvious change in the rate of progression of the CKD (ie, no acute deterioration, just steady progression).Patients with CKD and stage 1 AKI based on an absolute creatinine rise of ≥26 µmol/L but who have a relative rise of ≤15% in creatinine are regarded as stable CKD and therefore not eligible for the study.Children or young people <18 years of age.Patients in the terminal phase of malignancy or end-stage major organ disease where they have little potential to benefit from Outreach. These would typically be identified as having a life expectancy likely to be <3 months.Patients lacking mental capacity (unless enrolment agreed in writing with a personal consultee or nominated consultee (after phase) or personal consultee (before phase)).Other technical aspects of making alert not credible: inadequate data; suppressed creatinine at baseline.

It was impractical to take written informed consent from the large numbers of patients involved over two hospitals, when the study was focused on providing AKI Outreach to clinicians. Therefore, it was agreed with the research ethics committee that we would write to all enrolled patients giving them an ‘opportunity to dissent’ or ‘opt out’ of the study. The opt out letter will be sent to the patient's home address as soon as possible after enrolment. In conjunction with the opt out letter, a leaflet explaining AKI will be sent to patients in the intervention group only.

The study is registered at ClinicalTrials.gov (NCT02398682). It is funded by the Research for Patient Benefit programme of the UK National Institute for Healthcare Research (PB-PG-1111-26038) and sponsored by the Heart of England Foundation Trust. The trial has two phases and four groups (2 during each phase—see also figure 1):
The before phaseDuring the 2-month before phase, patients in the two groups will be observed for the outcome measures, without any intervention, thus defining outcomes with good standard care. There will be two before phase groups:
Heartlands and area patients—patients with AKI in secondary and primary care—observed only.Good Hope and area patients—patients with AKI in secondary and primary care—observed only.The after phaseDuring the 5-month after phase, the intervention will be delivered to the intervention group (Heartlands and area) only. There will be two after phase groups:Heartlands hospital and area patients—intervention provided for patients with AKI in secondary and primary care, mainly using Outreach via telephone (see below).Good Hope hospital and area patients—patients with AKI in secondary and primary care—observed only.

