#### Alerts

The electronic AKI alerts are the trigger for the afferent arm of the intervention. The alerts are generated within the laboratory software (Telepath, Computer Sciences Corporation) according to the national algorithm.^25^ It compares the current patient creatinine to a value in the past (baseline creatinine). The staging follows KDIGO guidelines for AKI,^26^ where 0 is no AKI and 3 is the most severe stage. Alerts are made visible to all users of the electronic patient records, with the stage being stated as part of all urea, creatinine and electrolyte reports. The alerts from our hospital laboratory also contain a hyperlink to online guidance, with separate guidance for hospital and community alerts. Alerts are not issued for patients in the dialysis units and renal wards. We refer to the current location of the patient when discussing community (primary care) or hospital alerts. Obviously some of the hospital alerts will represent what was community-acquired AKI, but Outreach focuses on the current location of the patient.

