### After phase sample size

For the before phase, no sample size is required and eligible patients during the study period will be recruited. The sample size was calculated with the intent of estimating uncertainty of outcomes, to inform the design of the future cluster trial. Our previous work suggested that the combined outcome would be seen in about 40% of patients having an alert. With a sample size of >1000 (intervention group—Heartlands and area, after phase), a 95% CI of width 6% (37% to 43%) can be calculated. A sample size of 370 (control group—Good Hope and area, after phase) will allow us to produce a 95% CI of width 10% (35% to 45%).

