### Statistical analysis

The focus of the study is to assess feasibility of all aspects prior to full-scale evaluation. The data collected in this pilot study will be used to assess the uncertainty of the primary outcome. Further analyses will separately compare the before and after arms at the intervention and control sites. We note that the intervention and control sites cannot be directly compared. The control site data will be used to assess any ‘system-wide’ change in AKI outcomes. Additionally, survival analyses will be carried out, examining time to first composite primary outcome, and Kaplan-Meier survival curves produced for each of the four groups. This pilot study is not powered to provide a full comparison of the before and after phases. Among the end points, the use of dialysis and frequency of non-dialytic AKI complications will give an indication of the safety of the intervention. We will analyse estimated Glomerular Filtration Rate (eGFR) and CKD stage at a group level and changes at individual patient level. We will also explore the potential of using these data to validate our previous prognostic index.^9^

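### Enrolment depends on clinicians ordering a creatinine test, and Outreach acts on those clinicians at Heartlands only, so the per-alert event rate there may shift in either direction through case ascertainment

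*Protocol article*

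**What the plan says.** Entry is the same in all four groups (Overall study design): "Patients will be recruited once they have an electronic alert indicating that they have AKI". Under Alerts, the laboratory software compares a current creatinine with an earlier value, so there is no alert without a test. Each patient can enter only once (Data collection and recruitment).

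Outreach is given in the after phase at Heartlands and its area only. It is mainly a telephone call to the team treating the alerted patient (Interventions), and its content includes diagnostic and monitoring advice (Intervention package). On randomisation, Overall study design says: "There will be no patient-level randomisation to avoid the risk of contamination, as this is a pilot for a CRT".

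The event rate is expressed per alerted patient (After phase sample size): "Our previous work suggested that the combined outcome would be seen in about 40% of patients having an alert". The composite is death, dialysis or progression of AKI stage within 30 days; progression can occur only from stage 1 or 2 (Outcomes). The planned comparison is: "Further analyses will separately compare the before and after arms at the intervention and control sites". The same section uses the control site to assess system-wide change, says the two sites cannot be directly compared, and says the study is not powered for a full before/after comparison.

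**The concern.** The denominator of the Heartlands comparison is people whom a clinician chose to test and whose result triggered an alert. In the after phase those clinicians receive advice about AKI, with more than 1000 patients planned over 20 weeks. If this changes whom they test, or when, the intervention changes who is in the analysed group. This is identification bias after allocation.

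Two effects are possible, and they oppose each other:

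- **Dilution.** More testing of patients not yet enrolled could add mild first alerts, and the rate per alert would fall with no patient doing better.
- **Detection.** Earlier testing could move a first alert from stage 3 to stage 1 or 2, after which worsening counts as an event. More repeat testing of enrolled patients would also find more progression. Both raise the rate.

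Good Hope receives no Outreach, so it can show a trust-wide change but not one confined to Heartlands. The limitations in the Discussion do not mention this. The stated aims include the value of Outreach on the measured outcomes and the supply of estimates for the cluster trial. Unless testing is measured, neither a fall nor a flat result at Heartlands can be read cleanly.

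**Working it through.** **Inputs from the article.** Event rate 40%; after-phase size above 1000 (Heartlands) and 370 (Good Hope), from After phase sample size; phases of 8 and 20 weeks, from Data collection and recruitment.

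**Assumed inputs.** The extra first alerts as a share of the original ones (x) and their event rate (e) are not in the article; x = 5-20% and e = 10-30% are used. The before-phase size is not fixed ("For the before phase, no sample size is required and eligible patients during the study period will be recruited"); about 400 at Heartlands is assumed, from 1000 × 8/20.

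**1. The article's own figures.** Half-width = 1.96 × √(0.40 × 0.60 / n).

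- n = 1000: 3.04 points, interval 36.96% to 43.04%. This agrees with "a 95% CI of width 6% (37% to 43%) can be calculated".
- n = 370: 4.99 points, interval 35.01% to 44.99%, which agrees with the stated width of 10%.

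**2. Dilution alone, no treatment effect.** After-phase rate = (0.40 + x·e)/(1 + x). The fall from 40%, in points, is in brackets.

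| x | e = 10% | e = 20% | e = 30% |
|---|---|---|---|
| 5% | 38.6% (1.4) | 39.0% (1.0) | 39.5% (0.5) |
| 10% | 37.3% (2.7) | 38.2% (1.8) | 39.1% (0.9) |
| 20% | 35.0% (5.0) | 36.7% (3.3) | 38.3% (1.7) |

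**3. Against the precision of the comparison.** The half-width for one group (3.04 points) is exceeded in 2 of the 9 cells. The relevant yardstick is the before/after difference: 1.96 × √(0.24 × (1/400 + 1/1000)) = 5.7 points. All nine cells lie inside it. With 400 before and 1000 after, the chance of a nominally significant result towards benefit is 9% at x = 10%, e = 20%, and 42% at x = 20%, e = 10%. With no shift it would be 2.5%.

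**4. The opposite effect.** Suppose extra testing raises detected progression in the original cases by d. The rate becomes (0.40 + d + x·e)/(1 + x), which returns to 40% when d = x(0.40 − e):

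- x = 10%, e = 20%: d = 2.0 points
- x = 20%, e = 20%: d = 4.0 points
- x = 20%, e = 10%: d = 6.0 points

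A larger d makes the after-phase rate higher than the before-phase rate, again with no true effect.

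**The case against.** **The mechanism is not stated.** No section says that Outreach raises testing in patients not yet alerted. The listed diagnostic items are volume status, dipstick, sepsis investigation and ultrasound, not creatinine. Calls follow an alert, concern that patient and are mostly single. Extra tests in an enrolled patient add nobody. All of this stands. A reader might take the sentence on contamination as an admission that clinicians will test other patients more, but it says nothing about whom they test. The spill-over is plausible, not documented.

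**The direction is open.** A reader might infer that the bias must favour Outreach. The article does not support that: it gives no event rates by stage, and its definition of progression lets earlier or repeat testing raise the composite.

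**It is a feasibility pilot.** The article disclaims power, defers the definitive answer to a cluster trial, and does not make a fall in the composite a criterion of success. The before-phase groups and Good Hope also give rates that Outreach cannot alter. This limits the consequence but does not remove it, because the Heartlands after-phase group is one of the two sized to inform the cluster trial, and a test of all study procedures is a natural place to check ascertainment. Whether the cluster trial would inherit the problem depends on how it recruits, which is not described.

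**A condensed article may leave such tabulations to the full protocol or SAP.** That is fair, and those documents may contain them. But the article itself fixes the entry route, the denominator, the within-site comparison and the control-site check, and together these do not reveal a change confined to Heartlands.

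**Conclusion.** The structural point holds: at Heartlands the intervention may alter who enters the denominator and how fully progression is detected, and the one stated check cannot show it. The direction is not fixed and the size is unknown. Under the assumed x and e, dilution alone lowers a 40% rate by 0.5 to 5.0 points, within the roughly 5.7-point half-width of the before/after difference, which itself rests on an assumed 400 before-phase patients. Modest increases in detected progression would cancel or reverse the fall. The documents do not support saying that Outreach will increase testing, or that a spurious benefit is the expected result. They support measuring testing and case mix, so that a change in the per-alert composite can be interpreted.

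**What to change.** 1. From the laboratory system, report creatinine tests, distinct adults tested and first AKI alerts by stage, for each site, location (hospital or community) and phase.
2. Add a before/after comparison stratified by, or adjusted for, first-alert stage.
3. Report death or dialysis within 30 days separately, since it depends less on testing than stage progression does.
4. Optionally, for hospital alerts, add events per 1000 emergency admissions, provided that enrolment of alerted patients is comparably complete in both phases. An outcome rate per adults tested should not be used, because extra testing inflates that denominator directly. For illustration, suppose 20% more adults tested yield 10% more alerts at a 20% event rate. Events rise by a factor of (0.40 + 0.10 × 0.20)/0.40 = 1.05, so the per-tested rate falls by 12.5% (1.05/1.20), against 4.5% for the per-alert rate (1.05/1.10).
5. State that if testing or first-alert stage mix shifts at Heartlands and not at Good Hope, the change in the per-alert composite will be reported as possibly due to case ascertainment and carried into cluster-trial planning with that caveat.

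The cost is a small amount of aggregate extraction and analysis and a few lines of text, with no patient contact. Stage adjustment may not fully remove the bias, because added cases may be milder within a stage and earlier testing can itself change the stage at entry.

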### Outcomes

The primary purpose of this study is to assess feasibility and inform a full cluster randomised study. The primary outcome for the full study, also collected in this study, is reflected in the trial acronym: deterioration or death of the patient with AKI, and is a combination of:
All-cause death within 30 days;Any need for dialysis or renal replacement therapy (intermittent haemodialysis (typically at the Renal Unit of Birmingham Heartlands Hospital) or continuous renal replacement therapy (typically in the intensive care units of the Trust)) within 30 days;Progression of AKI stage without dialysis within 30 days after the alert (stage progression is stage 1 deteriorating to 2 or 3; stage 2 deteriorating to stage 3).

These were chosen to reflect the major, potentially modifiable, outcomes of concern for patients (death and/or dialysis) and renal units or hospitals (death, dialysis or deterioration). Stage progression (compared to non-progression) is known to be associated with increased mortality and length of stay in a multivariate analysis,^34^ and is a useful surrogate end point.

Secondary outcomes for the main study, collected to assess feasibility here, are as follows:

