### Discussion and limitations of the study

The national algorithm for staging of AKI means that identification of patients with AKI is standardised. The ‘opt out’ consent process enables large-scale recruitment. The ethos of AKI Outreach is that advice is offered to the primary clinician, who may choose to act upon or ignore that advice. A key challenge in implementing the intervention is reaching and influencing the decision maker(s) within the primary team, especially as they have varying roles and beliefs.

The AKI Outreach service runs only 40 hours/week and not out-of-hours. As this is a pilot for a full CRT, there were only two sites and randomisation was not undertaken. Inevitably, the intervention and the control sites are different to a certain extent. The latter does not have on-site nephrology services. A full CRT is needed to provide a definitive answer regarding any benefits of this approach. What would a successful pilot look like? The delivery of recommendations acceptable to clinicians, comparable to our previous work (median of 3 within a median of 15 hours), and to large numbers of patients is a key indicator of success. The control group should show no evidence of a system-wide change in before and after AKI outcomes. The intervention group will provide evidence of the feasibility and safety of the intervention.

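### The death exclusion in Box 1 is tied to Outreach contact, which happens in only one of the four groups, so as written it drops early deaths from that group alone

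*Protocol article*

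**What the plan says.** Under Overall study design, the entry event is the alert: "Patients will be recruited once they have an electronic alert indicating that they have AKI". The Box 1 criteria are applied after that, as one list for all groups. The first exclusion is "Patient deceased at the time of Outreach team intervention". The second is "Patient already accepted for dialysis by HEFT renal unit", with no reference time given.

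The same section describes four groups. In the before phase, "patients in the two groups will be observed for the outcome measures, without any intervention". In the after phase the control group is again "Good Hope hospital and area patients—patients with AKI in secondary and primary care—observed only". Only Heartlands and its area in the after phase receive Outreach.

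The Outcomes section makes "All-cause death within 30 days" a component of the primary composite, together with renal replacement therapy and AKI stage progression. Only stage progression is explicitly timed from the alert. The Discussion states "The AKI Outreach service runs only 40 hours/week and not out-of-hours" and cites a median of 15 hours to recommendations in the team's previous work.

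The Statistical analysis section plans before/after comparisons within each site and Kaplan-Meier curves of time to first composite event for each of the four groups. The control site is used to look for system-wide change.

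**The concern.** An eligibility rule should act at time zero and in the same way in every group. This one acts after time zero, on an event that is part of the primary outcome, and refers to a moment that three of the four groups do not have. It is immortal time written into the entry criteria: a Heartlands after-phase patient must survive from alert to contact to be eligible, and an observed patient need not.

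Three uses of the data are exposed:

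- **Before/after comparison at Heartlands.** The after-phase rate falls relative to the before-phase rate without any effect of Outreach.
- **Kaplan-Meier curves.** The earliest deaths are missing from one curve of four.
- **The rate passed to the cluster trial.** The 40% planning figure refers to patients with an alert. Patients alive at contact are a different denominator.

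The control site offers no protection. The artefact is confined to Heartlands after, so Good Hope would show no change. The Discussion counts an unchanged control group as a mark of a successful pilot, so a spurious Heartlands improvement beside a flat control would look like an effect.

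**Working it through.** **Where the rule can operate**

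| Group | Outreach contact? | Death after the alert, before any contact (literal reading) |
|---|---|---|
| Heartlands, before | No | Counts as an event |
| Good Hope, before | No | Counts as an event |
| Heartlands, after | Yes | Patient excluded |
| Good Hope, after | No | Counts as an event |

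**Is there a window?** The service covers 40 of 168 hours, so 1 − 40/168 = 76% of the week is out of hours. The 15-hour median from previous work is a benchmark, not a forecast for this service, but it confirms that contact does not coincide with the alert.

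**The plan's own precision figures.** With a composite rate of 40% (After phase sample size) and the interval p ± 1.96 × √[p(1 − p)/n]:

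- n = 1000: √(0.24/1000) = 0.01549, giving 36.96% to 43.04%, width 6.07%. The article says 6%.
- n = 370: √(0.24/370) = 0.02547, giving 35.01% to 44.99%, width 9.98%. The article says 10%.

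Both reproduce. The point does not touch the sample size; it concerns what the estimated rate means.

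**Effect of the exclusion with no true effect.** Let f be the share of alerted patients who die before contact and are removed. All of them are outcome events, so f leaves both numerator and denominator:

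- observed rate = (0.40 − f)/(1 − f)
- shift = 0.40 − (0.40 − f)/(1 − f) = 0.60f/(1 − f)

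The article gives no value for f. Over an assumed range:

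| f (assumed) | Observed composite | Shift, points |
|---|---|---|
| 0.5% | 39.7% | 0.3 |
| 1% | 39.4% | 0.6 |
| 2% | 38.8% | 1.2 |
| 3% | 38.1% | 1.9 |
| 5% | 36.8% | 3.2 |

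The shift is about 0.6 points per 1% removed. It equals the planned 3-point half-width when 0.60f/(1 − f) = 0.03, that is f = 0.03/0.63 = 4.8%.

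**Death alone.** With 30-day mortality m, the shift is (1 − m)f/(1 − f). Death is a component of the composite, so m cannot exceed the composite rate, and the shift in mortality is at least as large as the shift in the composite.

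**The case against.** **This is a feasibility pilot.** The article says that it lacks the power for a full before/after comparison, that the two sites cannot be directly compared, and that a cluster randomised trial is needed for a definitive answer. This stands and limits the consequence. It does not remove the asymmetry, because the comparisons and curves are still planned and the outcome rate is still meant to inform the next trial.

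**Early deaths may be missed in the observed groups too.** Under Data collection and recruitment, patients are moved from the alert list into the study database at enrolment, without distinction by group. An observed patient who dies before staff enrol them might also be lost. The article does not say how this is handled, so one cannot be certain that every such death counts in the other three groups. That is a further reason to state one rule. It also means excluded patients may not be in the database at all, so a later analysis plan might be unable to restore them.

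**Stronger readings that the article does not support:**

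- *All eligibility is checked at contact.* Only the death criterion carries the Outreach time; the general rule is that criteria follow the alert.
- *Early dialysis acceptances also leave one group only.* The dialysis criterion has no Outreach anchor and is written for all groups. Its defect is an unstated reference time, which becomes a bias only if the check is made later in the Heartlands after group.
- *The terminal-illness exclusion is applied after speaking to the clinician, in one group only.* Nothing in the article says so.
- *The size can be worked out.* A reader might take 23% as 30-day mortality and a mean wait of 15.2 hours, which follows from assuming five 8-hour days and alerts spread evenly over the week. A constant hazard then gives f of about 0.55%, and an assumed fivefold early hazard gives 2.73%, or about 2.2 points of apparent mortality benefit. But the Background gives overall mortality above 23% with no 30-day window, and the early-hazard multiplier has no source. The mean of 15.2 hours does not corroborate the 15-hour median either: setting [4(16 − t) + (64 − t)]/168 = 0.5 gives a model median of 8.8 hours.

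**Conclusion.** The point holds for the death criterion. Followed as written, it removes deaths between alert and contact from the Heartlands after-phase group and from no other. With no true effect, that lowers both the death rate and the composite rate there, always in favour of Outreach.

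The direction rests on the literal wording and on such deaths being counted in the observed groups. The size is not established: about 0.6 points of the composite for each 1% of alerted patients removed, from the 40% planning rate, with f unknown. A small f would leave the shift well inside the planned 3-point half-width.

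This is a should-fix. It affects the before/after comparison, the Kaplan-Meier curves and the rate passed to the cluster trial. It does not affect the feasibility aim or the stated sample-size precision.

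**What to change.** - Reword the death criterion so that it excludes only patients who had died by the time the alert was issued, or by one common landmark after it, identically in all four groups.
- Keep Heartlands after-phase patients who die after that point but before contact in the analysis, recorded as 'not reached'.
- Start the 30-day clock for every outcome component, and the time-to-event analysis, at the alert.
- Give the dialysis-acceptance criterion the same explicit reference time.
- Report the number excluded by criterion and by group.

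The remaining exclusions, including mental capacity and terminal illness, need not be frozen at the alert. Mental capacity could not easily be, because it involves written consultee agreement. They should be applied by the same procedure in all groups.

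The cost is small: a change of wording in Box 1, a statement of the analysis population, and a table of exclusions. The downside is that a few uncontacted patients slightly dilute the apparent effect of Outreach.
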